## **ABSTRACT**

Intestinal constipation is one of the most prevalent non-motor symptoms of Parkinson's disease (PD), negatively impacting quality of life and treatment adherence. Evidence suggests that healthy dietary patterns may contribute to relieving these symptoms and modulating gut microbiota. However, there is a lack of clinical trials investigating the impact of nutritional interventions in patients with PD. In this context, the NUTRI-GUT-PD research project aims to evaluate the effect of a nutritional intervention on constipation symptoms in individuals with PD. This is a randomized controlled clinical trial including participants diagnosed with PD and functional constipation. Participants will be randomly assigned to one of two groups: (1) a nutritional intervention group, consisting of an individualized meal plan and follow-up with a nutritionist for three months, and (2) a control group, which will receive nutritional guidance only at the end of the study period. The nutritional intervention will be based on the Dietary Reference Intakes (DRIs), in combination with recommendations from the literature for the management of PD-specific nutritional needs and constipation symptoms. Assessments will be conducted at baseline, midway, and at the end of the intervention period. The following outcomes will be evaluated: weekly bowel movement frequency, stool consistency (Bristol Stool Scale), constipation symptoms using the Constipation Scoring System, gut microbiota composition, dietary intake, diet quality, nutritional status, and clinical parameters related to PD. At the end of the study, it is expected that the nutritional intervention will lead to improvement in constipation symptoms, greater gut microbial diversity, improved diet quality, and better nutritional status among participants.

**Keywords:** Parkinson's disease; Constipation; Gut microbiota; Nutritional counseling; Healthy diet.

## **LIST OF ABBREVIATIONS AND ACRONYMS**

BIA – Bioelectrical Impedance Analysis

AC – Abdominal Circumference

AC – Arm Circumference

CEP – Research Ethics Committee

CC – Calf Circumference

CPC – Clinical Research Center

CSS – Constipation Scoring System

PD – Parkinson's Disease

HS – Handgrip Strength

HCPA – Porto Alegre Clinical Hospital

BMI – Body Mass Index

MAN-VR – Mini Nutritional Assessment – Reduced Version

MDS-UPDRS – Movement Disorder Society – Unified Parkinson's Disease Rating Scale

MoCA – Montreal Cognitive Assessment

NOVA-UPF – Nova Ultra-processed Foods

NOVA-WPF – Nova Whole Plant Foods

PPGCM - Graduate Program in Medicine: Medical Sciences

24hFR – 24-hour Food Recall

SARC-F – Sarcopenia Screening Tool

SDQ – Swallowing Disturbance Questionnaire

TACO – Brazilian Table of Food Composition

ICF– Free and Informed Consent Form

GI– Gastrointestinal Tract

TUG – Timed Up and Go

## 1. INTRODUCTION

Parkinson's Disease (PD) is a progressive neurodegenerative disease that affects the central nervous system (CNS) and is currently the most prevalent movement disorder in the world (Balestrino; Schapira, 2020; Dorsey et al., 2018; Pringsheim et al., 2014). The prevalence of the disease has been increasing globally in recent decades, and between 1990 and 2015 it rose to 6.2 million people with PD (Dorsey et al., 2018a, 2018b). In Latin America and the Caribbean, the prevalence of PD is 1,081 per 100,000 inhabitants (Pereira et al., 2024).

The disease is characterized by motor symptoms such as: tremor, bradykinesia, rigidity, and postural instability, which result from the degeneration of dopaminergic neurons in the substantia nigra of the brain and the depletion of striatal dopamine (Tolosa et al., 2021). In addition to this, PD presents with non-motor symptoms (NMS) that are particularly complex as they involve multiple brain regions and the participation of other neurotransmitters (Munhoz et al., 2015). These manifestations include hyposmia, constipation, urinary dysfunction, orthostatic hypotension, memory loss, depression, pain, and sleep disturbances (Pont-Sunyer et al., 2015; Tolosa et al., 2021). Constipation emerges as one of the most reported symptoms by people with PD, being mentioned in 20% to 89% of cases, which represents an incidence 2 to 4 times higher than in the general population (Pfeiffer, 2011).

The term "constipation" is often used generically to define any difficulty with evacuation. However, functional constipation is defined by the Rome IV criteria as persistent symptoms of unsatisfactory evacuation in the absence of identifiable organic causes (Drossman; Hasler, 2016). In PD, constipation results from pathophysiological impairment of colonic motility that affects the entire gastrointestinal tract (GIT). The literature has suggested that the gut may be one of the initial sites of PD pathophysiology, as proposed by the Braak hypothesis, which suggests the retrograde transmission of pathological alpha-synuclein from the gastrointestinal tract to the CNS via the vagus nerve (Yemula et al., 2021). Individuals with chronic constipation have a 3 to 11 times higher risk of developing PD, and data from prospective and retrospective studies suggest that constipation becomes evident on average between 15.6 and 24.0 years before diagnosis (Postuma et al., 2013; Yu et al., 2018).

Constipation may also be related to changes in the composition of the gut microbiota, which has been increasingly recognized as part of the pathophysiological process of PD. Evidence suggests that patients with PD have a reduction in microbial diversity and an imbalance between beneficial and potentially pathogenic bacteria, known as dysbiosis (Salim et al., 2023). This imbalance can contribute to increased intestinal permeability, activation of the immune system, and chronic inflammation, factors that are associated with the progression of neurodegeneration. The gut microbiota also communicates with the central nervous system through the microbiota-gut-brain axis, influencing gastrointestinal motility, neurotransmitter synthesis, and the function of epithelial and blood-brain barriers (Uyar; Yildiran, 2019).

Some dietary factors, such as excessive consumption of ultra-processed foods, which are rich in additives and low in fiber, can further compromise gut health, aggravating dysbiosis and contributing to constipation (Song et al., 2023). A cross-sectional study identified that the microbiota pattern in PD patients was related to eating habits and that a healthier diet can increase the abundance of bacteria with potential anti-inflammatory effects, while reducing the presence of bacteria with a pro-inflammatory profile in PD patients. Suggesting that consuming a good quality diet can contribute to controlling pro-inflammatory dysbiosis in these patients and possibly offer some protection against disease progression (Kwon et al., 2024).

A study conducted by Barichella et al. (2017) analyzed the eating habits and neurological characteristics of 600 people with PD compared to 600 healthy controls. The results showed that individuals in the PD group had a lower BMI, higher caloric and protein intake, and a higher prevalence of constipation. Constipation was reported by 46.8% of PD patients, which was significantly higher than the controls (6.8%). Despite a higher fiber intake than controls, water intake was considerably lower, which may compromise the effects of fiber on intestinal function. Furthermore, constipation was associated with higher doses of levodopa, suggesting that changes in intestinal transit and microbiota may reduce the bioavailability of the drug. The study reinforces the importance of including systematic nutritional assessment in the multidisciplinary management of the disease, with a special focus on weight control, constipation management, and adequacy of protein intake to optimize therapeutic efficacy (Barichella et al., 2017).

Several strategies have been proposed in randomized clinical trials (RCTs) to reduce constipation symptoms and improve microbiota diversity in PD patients. Most focus on the use of probiotics or specific drugs with a laxative effect. Probiotics in general demonstrate quite positive effects, with increased bowel frequency, improved stool consistency, decreased intestinal transit time, reduced use of laxatives, improved quality of life, and also improved microbiota (Du et al., 2022; Ibrahim et al., 2020; Tan et al., 2021; Yang et al., 2023). The intervention time in these studies ranged from 8 to 12 weeks with daily consumption, sometimes several times a day, of the proposed probiotic. Medications with a laxative effect also showed safety and positive results in improving constipation symptoms (Hatano et al., 2024; Kubo et al., 2024; Ondo et al., 2012; Parkinson Study Group, 2017; Zangaglia et al., 2007). However, the long-term effect of continuous use of these probiotics and medications is unknown. In contrast, these strategies may not be feasible in diverse socioeconomic contexts.

We identified only one RCT that performed dietary intervention, implementing the Mediterranean diet (Rusch et al., 2024). This study compared a group that received standard treatment (recommendations on physical activity, fiber and liquid consumption, and use of laxatives) with a group that received standard treatment associated with the Mediterranean diet. Both interventions

reduced constipation symptoms, although the change was not significantly different between the groups.

Given this scenario, diet has gained prominence as a promising non-pharmacological intervention in the management of PD. Studies suggest that healthy eating patterns may be associated with improved motor and non-motor symptoms, in addition to contributing to the maintenance of patients' functionality and autonomy (Rees et al., 2024). However, it is observed that the diet quality of individuals with PD is often inadequate, characterized by high consumption of ultra-processed foods and low intake of fiber and essential micronutrients (Dunk et al., 2023; Kwon et al., 2023).

Nutritional monitoring emerges not only as support for pharmacological treatment but as a potential therapeutic intervention to improve intestinal function and the quality of the microbiota of these individuals. Despite advances, randomized clinical studies that structurally evaluate the impact of nutritional interventions for people with PD are still scarce. Thus, investigation through RCTs of the effect of this monitoring on constipation symptoms and microbiota diversity is necessary.

## **2. JUSTIFICATION**

Constipation is one of the most prevalent NMS in PD, impacting the gut microbiota and the effectiveness of drug therapy, in addition to being associated with clinical complications such as abdominal distension and increased risk of intestinal perforation (Cirstea et al., 2020; Yemula et al., 2021). Although there are RCTs on pharmacological approaches and the use of probiotics with positive results, these strategies may present limitations regarding economic feasibility, long-term adherence, and safety, especially in populations with less access to health resources (Hatano et al., 2024; Tan et al., 2021).

Given this scenario, interventions based on healthy eating gain relevance because they are low-cost, culturally adaptable, and have potential benefits in various other aspects. Growing evidence suggests that dietary patterns rich in fiber, micronutrients, and whole foods can contribute not only to improving constipation symptoms but also to the positive modulation of the gut microbiota, a factor that has been studied in the pathophysiology of PD (Kwon et al., 2023; Pourmotabbed et al., 2025; Song et al., 2023).

Despite this, there is still a gap in the literature regarding the contribution of nutritionists to the care of patients with PD. The literature already highlights several nutritional particularities of this population, such as the interaction between dietary protein and levodopa, frequent weight loss and the risk of malnutrition, in addition to dysphagia and constipation. However, more studies are still needed to substantiate more robust guidelines on the recommended nutrient quantities for these patients.

Thus, the research question arises: In individuals with PD and functional constipation, is nutritional intervention with a nutritionist's follow-up effective in reducing constipation symptoms and modulating the gut microbiota? This study intends to contribute to the production of nutritional guidelines in the care of people with PD, offering a safe, accessible, and sustainable therapeutic alternative for the management of constipation.

### **3. OBJECTIVES**

#### **3.1 Primary Objective**

To evaluate the efficacy of a nutritional intervention with dietitian follow-up on the number of bowel movements per week in individuals with Parkinson's Disease and functional constipation.

#### **3.2 Secondary Objectives**

1. To evaluate the effect of the nutritional intervention compared to the control on the intestinal microbiota composition of people with PD;
2. To relate the clinical aspects of PD with the intestinal microbiota composition;
3. To evaluate the food intake and diet quality of people with PD, as well as the effect of the nutritional intervention on these parameters;
4. To evaluate the nutritional status of patients with PD and the effects of the nutritional intervention on this outcome;
5. To identify the clinical characteristics associated with the effect of the nutritional intervention in patients with PD.

### **4. METHODS**

#### **4.1 Design**

This is a 3-month (90 days) parallel randomized clinical trial to be conducted at Hospital de Clínicas de Porto Alegre (HCPA) (SPIRIT 2025 checklist - APPENDIX A)

#### **4.2 Participants and recruitment**

Recruitment of participants for the NUTRI-GUT-PD study will be carried out from the LARGE-PD study database (2024-0445). LARGE-PD participants linked to HCPA are invited during in-person appointments at the Parkinson's Disease and Movement Disorders Research Group. Participants outside the institution can volunteer by filling out a questionnaire available in the promotional material. The outpatient clinic has a broad and consolidated base of regularly followed-up patients, which facilitates access to the necessary number of eligible participants.

Participants of LARGE-PD evaluated in the last three months who have the marking “Patient agrees with LGPD Consent Form” and who meet the inclusion and exclusion criteria will be considered for NUTRI-GUT-PD. These participants will be contacted by phone for a formal invitation and, if they accept, a room will be scheduled at the CPC for the detailed explanation and in-person signing of the Informed Consent Form (ICF – APPENDIX B). It will also be possible to invite LARGE-PD participants immediately after their evaluation at the CPC, checking their interest in joining NUTRI-GUT-PD and, if positive, the ICF will be applied in person. All those who accept will be included after signing the ICF.

#### 4.2.1 Inclusion Criteria

Adults with a prior diagnosis of Parkinson's Disease, confirmed by a neurologist based on the Movement Disorders Society criteria (Postuma et al., 2015), and who have been on a stable dose of levodopa for at least 3 months will be included. Furthermore, participants must report at least two of the criteria defined by the Rome IV protocol for the characterization of Functional Constipation (Drossman; Hasler, 2016):

- Straining during more than 25% of defecations;
- Lumpy or hard stools (Bristol Stool Form Scale types 1–2) in more than 25% of defecations;
- Sensation of incomplete evacuation for more than 25% of defecations;
- Sensation of anorectal obstruction or blockage for more than 25% of defecations;
- Need for manual maneuvers to facilitate defecation (e.g., digital evacuation, support of the pelvic floor) in more than 25% of defecations;
- Fewer than three spontaneous bowel movements (SBM) per week;
- Loose stools are rarely present without the use of laxatives;
- Insufficient criteria for irritable bowel syndrome;

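### As written, section 4.2.1 lets a patient with none of the six constipation symptoms qualify, because rarely having loose stools and not meeting IBS criteria count towards the required two

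*Protocol*

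**What the plan says.** Protocol section 4.2.1 sets the only constipation requirement for entry: "participants must report at least two of the criteria defined by the Rome IV protocol for the characterization of Functional Constipation". Eight bullets follow at one level. The first six describe symptoms: straining, hard stools, incomplete emptying, blockage, manual help, and low frequency ("Fewer than three spontaneous bowel movements (SBM) per week"). The seventh is "Loose stools are rarely present without the use of laxatives" and the eighth is "Insufficient criteria for irritable bowel syndrome". No word or layout separates these two from the six above.

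The intended population is stated elsewhere. The Abstract says "This is a randomized controlled clinical trial including participants diagnosed with PD and functional constipation". Section 3.1 puts the primary objective as the effect on the "number of bowel movements per week in individuals with Parkinson's Disease and functional constipation". The Introduction says that "functional constipation is defined by the Rome IV criteria as persistent symptoms of unsatisfactory evacuation in the absence of identifiable organic causes".

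**The concern.** The threshold of two applies to all eight bullets, but the last two are not symptoms. They describe the absence of something, and a person with regular, easy, formed stools can satisfy both. The rule therefore fails in two directions:

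- A person with none of the six symptoms can qualify on the last two items alone, and a person with a single symptom can qualify by adding either of them.
- The last two items no longer act as requirements. A person who meets IBS criteria or often has loose stools can enter on any two symptoms.

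The primary outcome is weekly bowel movement frequency. Participants without constipation have little or no room to gain on it, so enrolling them would dilute the difference the trial is powered to detect. The conclusion would also no longer apply to the population in the primary objective. Enrolment errors of this kind cannot be undone afterwards in an intention-to-treat analysis of about 54 people.

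**Working it through.** **Is the gap closed elsewhere in the Protocol?**

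- Section 4.2 considers database participants who meet the inclusion and exclusion criteria, and includes those who accept once they have signed consent. It adds no separate diagnosis of constipation.
- Section 4.2.2 mentions constipation once, in exclusion 7, which removes constipation secondary to another condition. It does not remove a person without constipation, and it does not exclude IBS.
- No minimum severity score or maximum baseline bowel frequency is required.
- Recruitment is from a general Parkinson's database. The Introduction itself cites constipation in 46.8% of patients in one study and in 20% to 89% of cases overall, so unconstipated candidates are likely to be in the pool.

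**Counting the rule as written** (eight yes/no items, at least two needed)

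- Pairs of items: C(8,2) = 28. Pairs made only of symptoms: C(6,2) = 15. Pairs with at least one non-symptom item: 28 − 15 = 13, of which 6 × 2 = 12 have one symptom and 1 has none.
- Full answer patterns: 2^8 = 256. Eligible: 256 − 1 − 8 = 247.
- Eligible with no symptom: 1. Eligible with exactly one symptom: 6 × 3 = 18. Together, 19 eligible patterns have fewer than two symptoms.
- Patterns with at least two of the six symptoms and both remaining items met: 2^6 − 1 − 6 = 57.

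These are counts of combinations, not of patients.

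**Reproducing the plan's sample size** (section 4.5: difference 1 movement/week, SDs 1.15 and 1.21, 80% power, 5% significance taken as two-sided, 90% retention at time point 2, correlation 0.5)

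- Complete data: (1.96 + 0.8416)² × (1.15² + 1.21²) / 1² = 21.87 per arm.
- Retention factor with two time points: (1 − 0.5²)/0.9 + 0.5² = 1.0833.
- 21.87 × 1.0833 = 23.7, so 24 per arm and 48 in total; 48/0.9 = 53.3, so 54. Both of the plan's figures reproduce.

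**Dilution.** Suppose a share q of participants gains nothing and the others gain 1 movement/week, with the SDs unchanged. The expected difference is then 1 − q.

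- SE with 24 per arm = √[(1.15² + 1.21²) × 1.0833 / 24] = 0.3547.
- Power = Φ[(1 − q)/0.3547 − 1.96].

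| Assumed share q | Difference | 24 per arm, 90% retained | 24 per arm, all analysed | 27 per arm, 90% retained |
|---|---|---|---|---|
| 0 | 1.0 | 0.805 | 0.835 | 0.85 |
| 10% | 0.9 | 0.718 | 0.752 | 0.77 |
| 20% | 0.8 | 0.616 | 0.651 | 0.67 |
| 30% | 0.7 | 0.505 | 0.538 | 0.55 |

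The fourth column omits the retention factor (SE = √[2.7866/24] = 0.3408). The last uses the inflated target of 27 per arm with the factor kept (SE = √[2.7866 × 1.0833/27] = 0.3344).

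**The case against.** The strongest reply is that the intent is plain. The rule refers to the Rome IV characterization of functional constipation, and the Abstract, the Introduction and section 3.1 all fix the population. Whether someone has insufficient criteria for IBS is an assessor's judgement rather than something a participant reports, so a trained assessor may well treat the last two bullets as conditions. On this view the defect is an ambiguous list whose meaning can be recovered. The intent is indeed recoverable, and nothing shows that anyone would in fact be enrolled wrongly. But eligibility is decided on the written rule. Staff who applied the intent would be departing from the text, and staff who applied the text would recruit the wrong population.

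Other objections stand in part:

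- The pair count does not measure harm. Twelve of the 13 pairs still include a symptom, and only one has none.
- The Protocol gives no basis for shares of 10% to 30% or for zero gain in such participants. The 80/72/62/50 series also starts from 24 per arm. With the planned 27 it is about 85/77/67/55, a drop of similar size from a higher start.
- The corrected rule does not guarantee room to improve. A participant who strains and feels incompletely emptied qualifies properly and may already have normal frequency. Correcting the rule secures the population, not a low baseline.

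None of these points removes the eligibility defect.

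**Conclusion.** The concern holds. On the Protocol's own text, the inclusion rule admits a person with no constipation symptom and does not enforce the two items that should apply to everyone. It conflicts with the Abstract, the Introduction's definition and the primary objective. This follows from the wording alone and needs no prevalence figure.

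The effect on the trial's result is illustrative. For every 10% of participants who cannot gain, power falls by roughly 8 to 12 percentage points, whichever of the three sample-size bases is used. That rests on an assumed share, zero gain in that share, the planned gain in everyone else, the plan's SDs unchanged, and a normal approximation.

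**What to change.** Rewrite the constipation requirement in section 4.2.1 as three conditions joined by AND: at least two of the first six (symptom) items; loose stools rarely present without laxatives; and insufficient criteria for irritable bowel syndrome. Use the same logic in any screening form or telephone script, and record each item so that eligibility can be checked.

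The cost is one sentence and the matching screening material, with an ethics amendment if the Protocol has already been approved. There is no new visit and no change to the endpoint or the analysis. The downside is a narrower entry rule: besides people without constipation, those with only one symptom and those with IBS or frequent loose stools become ineligible. The Protocol gives no figures from which to estimate how many candidates that would remove, so the recruitment forecast should be checked against the database under the corrected rule.
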